## Abstract

**Background:**

Children and adolescents growing up in child welfare institutions have been frequently exposed to traumatic events and psychosocial stress and show elevated rates of mental disorders. Yet, there is a lack of empirically supported treatments to provide adequate mental health care for children in care suffering from trauma-related mental disorders such as posttraumatic stress disorder (PTSD), depression, and anxiety. The Cognitive Behavioral Intervention for Trauma in Schools (CBITS) is an evaluated trauma-focused cognitive-behavioral group intervention, which has proven to be effective in reducing symptoms of PTSD, depression, and anxiety for traumatized children in group settings. The trial will evaluate the effectiveness of the CBITS intervention as an outreach treatment compared with an enhanced treatment-as-usual condition (TAU +) within the German mental health and child welfare system.

**Methods:**

In a randomized controlled trial (RCT) involving *N* = 90 children and adolescents, we will compare CBITS with TAU + . Participants between 8 and 16 years, reporting at least one traumatic event and moderate posttraumatic stress symptoms (PTSS), will be randomized within their child welfare institution to either one of the conditions using a CATS-2 severity-stratified block randomization. Assessments will take place at baseline, as well as 4 months and 10 months after baseline. The primary outcome is the severity of PTSS after 4 months. Secondary outcomes are depression, anxiety, irritability/anger, quality of life, and global functioning level.

**Discussion:**

The results of our trial will provide evidence regarding effective treatment options for traumatized children in care, which represent an understudied population with limited access to mental health care. Additionally, it could serve as a blueprint for implementing trauma-focused outreach group treatments for children in care and increase the accessibility to appropriate treatment.

**Trial registration:**

Clinical Trials.gov NCT06038357 D. September 13, 2023.

**Supplementary Information:**

The online version contains supplementary material available at 10.1186/s13063-024-08190-x.

## Background

Children and adolescents in (inpatient) child welfare and care institutions (dt. “Kinder- und Jugendhilfeeinrichtungen”) are probably the group in our society that is or has been exposed most frequently to extreme psychosocial stress and sequential traumatization. A study by Jaritz et al. [1] found that 75% of the children and adolescents in child welfare programs and care institutions in Germany had experienced at least one traumatic experience in their lifetime, while 51% had experienced various different kinds of traumatization. Additionally, crucial psychosocial and biological risk factors for the development of mental health problems (such as premature birth, prenatal exposure to noxious substances, and genetic predispositions) accumulate in this population [2]. As a consequence, mental health problems and, in particular, trauma-related mental disorders are significantly more common in child welfare populations than in the general population [3]. Several studies focusing on adolescents in foster care reported lifetime prevalence rates for posttraumatic stress disorder (PTSD) of 14–16% based on structured diagnostic interviews (e.g., [4]).

Recent meta-analysis [5] and international treatment guidelines [6] highly recommend trauma-focused cognitive behavioral approaches to treat PTSD and comorbid trauma-related disorders such as depression or anxiety disorders in traumatized children and adolescents. The individual treatment “trauma-focused cognitive behavioral therapy” (TF-CBT; [7]) is one of the treatments with the most empirical support worldwide and was found to be effective in German routine clinical care as well [8]. Next to a large body of evidence on the effectiveness of individual treatments, there is growing evidence on the feasibility and efficacy of trauma-focused group treatments. In fact, school- and community-based interventions in a group setting are one way of meeting the high demand for mental health care in vulnerable populations [9]. A recent meta-analysis by Davis et al. [10] examined the effectiveness of group-based interventions in reducing PTSD symptoms in 6–18-year-old children and adolescents. In total, they included 42 studies (*N* = 5998). The researchers found that participants in the group-based intervention had significantly fewer PTSD symptoms and improvement in depressive symptoms compared with control groups (PTSD symptoms: *g* =  − 0.55, CI [− 0.76, − 0.35]). Particularly, cognitive-behavioral interventions were effective in treating PTSD symptoms, especially in children and adolescents who experienced complex trauma (such as war experiences or sexual abuse). These interventions were often delivered by less trained staff or with translated versions of the manual and still demonstrated effectiveness.

One of the most researched trauma-focused cognitive-behavioral group interventions is “Cognitive Behavioral Intervention for Trauma in Schools” (CBITS; [11]), which has been scientifically evaluated and sustainably implemented across many regions in the USA, Australia, China, Japan, and Guyana. So far, the intervention has been evaluated in school settings in the USA and demonstrated promising results in a first pilot-test quasi-experimental study (*N* = 199 children; ages 8–15) in which CBITS was compared with a control condition (PTSD: *d*_pre-post/_CBITS_ = 0.67; *d*_Korr_ = 0.44; depression: *d*_pre-post_CBITS_ = 0.39; *d*_Korr_ = 0.34) [12] and a following RCT (*N* = 126 children; ages 10–12 years) regarding PTSD (reported effect size of 1.08 SDs) and depression (reported effect size of 0.45 SDs) at 3-month follow-up [13]. A field trial after Hurricane Katrina in New Orleans [14] (*N* = 118 children; ages 9–15, 55.9% female) showed significant results in terms of reduction in PTSD and depression among those who participated in CBITS (*n* = 57; *d*_PTSD_ = 0.72; *d*_depression_ = 0.42) and those who participated in trauma-focused cognitive behavioral therapy (TF-CBT) (*n* = 14; *d*_PTSD_ = 1.16; *d*_depression_ = 0.47). Although students who received the interventions improved in both arms of the study, uptake of the intervention was uneven across the groups, with 98% starting CBITS and only 37% beginning TF-CBT at a nearby clinic. This finding highlights the importance of low-threshold accessibility of an intervention as well as the high feasibility of CBITS.

So far, CBITS has not been evaluated in the German mental health system and in child welfare settings. Solely one study by Auslander et al. [15] adapted and implemented “Girls Aspiring toward Independence” (GAIN), a trauma-focused, group-based therapy which is an extended version of CBITS for girls in child welfare. They included *N* = 27 girls (12–18 years old) and randomized them either to an experimental or usual care condition. The results showed, despite the small sample size, significant symptom reductions (PTSS and depression) in the intervention group and lower reductions in the control condition. However, in a subsequent RCT [16], evaluating the intervention with adolescent girls (*N* = 249) in the child welfare system in the USA, PTSD, and depression decreased in both conditions, but the intervention was not superior to usual care. Only in regard to clinical improvement more participants in the intervention condition reported PTSS and depression symptoms under the clinical threshold post-intervention, compared to usual care. They found that the intervention was an acceptable model for the population though.

In sum, despite the results of the studies with (slightly older) girls in child welfare by Wendy Auslander and colleagues, CBITS seems especially appropriate for traumatized children in child welfare due to the (cost-effective) group component, low-threshold accessibility, and because the program focuses on reducing trauma symptoms and providing skills to handle stress and trauma in the future.

There is a shortfall between the mental health needs of the high-risk population in German child welfare programs and the treatment options made available to them. Due to several individual (e.g., self-stigma) and structural (e.g., lack of trained therapists in trauma-focused evidence-based treatments (EBTs), limited coordination between mental health professionals and child welfare staff) barriers, this large number of traumatized children has very little access to evidence-based trauma-focused care. Outreach treatments in which the therapist would travel to individuals, families, or child welfare programs to deliver the treatments have been recommended as this lowers the psychological and practical barriers to treatment [17]. In fact, until today, “Mein Weg” (Engl. “My Way”) for traumatized refugee minors is the only trauma-focused group treatment that has been systematically implemented, evaluated, and disseminated in child welfare programs in Germany [18].

The present study therefore aims at evaluating CBITS in the German mental health care system and systematically implementing it into routine care at child welfare institutions. Within the randomized controlled trial (RCT), trauma-exposed children with at least moderate posttraumatic stress symptoms (PTSS) will be randomized to either CBITS (intervention group) or treatment as usual enhanced (TAU + ; control group) in their child welfare institution stratified by CATS-2 severity. All participants will be assessed at baseline (T0), at 4 months (T1), and 10 months (T2) follow-up to evaluate the effectiveness of the intervention regarding symptom reduction compared to the control condition, on the one hand, and the feasibility of the group intervention within child welfare programs, on the other hand. In sum, not only the delivery of an evidence-based group program, but also the outreach engagement strategy is absolutely novel in the German health care service context. We expect that such a strategy will significantly improve access to EBTs, engagement in therapy, and outcomes of children and adolescents exposed to trauma and consequently help to decrease individual and societal costs of victimization during childhood and adolescence in the long term.

## Methods

### Aims and hypotheses

We aim to evaluate the intervention CBITS for children and adolescents being cared for in German child welfare programs and to systematically implement the intervention into routine care. The objectives are as follows:Primary objective: Evaluate the effectiveness of CBITS compared to TAU + regarding PTSS symptom reduction (primary outcome), anxiety, depression, irritability/anger, quality of life and functional level, and continuance of the child welfare program (secondary outcomes) at 4-month follow-upInvestigate potential long-term effects of the treatment in the treatment condition regarding the primary and secondary outcomes at 10-month follow-upImplement CBITS as an outreach intervention into routine mental health care for traumatized children, to evaluate treatment fidelity and treatment completion and investigate different potential individual or structural factors that might have an impact on the implementationTo assess the readiness of child welfare programs to collaborate with mental health services and the role of institutional environments for developmental trajectories

We expect CBITS to be superior to TAU+ regarding mental health outcomes, quality of life, functional impairment, and continuance of the child welfare program. Based on the current literature, we propose the following hypothesis regarding our primary objective:

H1: The CBITS intervention is superior in reducing PTSS compared with the control condition (TAU+) post-intervention.

The following secondary hypotheses will be tested in an exploratory manner:

H2a: The CBITS intervention is superior in reducing depression, anxiety, and irritability/anger compared with the control condition post-intervention.

H2b: The CBITS intervention is superior regarding improvements in quality of life, functional impairment, and continuance of the child welfare program compared with the control condition post-intervention.

H3: Symptom reduction within the CBITS intervention group is stable until 10-month follow-up post-intervention.

### Trial design

The current study is a randomized controlled trial with two active conditions (CBITS vs. TAU +) and three measurement time points. An independent institution (Institute of Epidemiology and Medical Biometry, Ulm University) will perform the randomization. The randomization will be conducted within each child welfare program. Hence, half of the participants within the program will be in the CBITS condition and the other half will be in the TAU + condition. Randomization will be done in the group of registered participants as CATS-2-stratified block randomization using the randomization software ROM [25]. Participants will be randomized in either CBITS or TAU + after their agreement to participate in the study and after the screening (T0) of participants of the respective facility is completed. The participants and their CATS-2 severity score will be reported as a list and will be sent to the Institute of Epidemiology and Medical Biometry for randomization. See Fig. 1 for participant flow through the study.

**Fig. 1 Fig1:**
[figure not shown]
Participant flow through the study

The study protocol was written in accordance with the SPIRIT 2013 statement (Standard Protocol Items: Recommendations for Interventional Trials; for the SPIRIT Checklist see Additional file 1, for SPIRIT Table see Table 1).

**Table 1 Tab1:**
[figure not shown]
SPIRIT table

### Study setting and recruitment

As this is an outreach study, assessment and intervention will take place outside of the clinical setting: the child welfare facilities in which the children and adolescents live. Researchers from a university clinic will be involved in instructing screenings and implementing the intervention (workshop, case consultation).

Recruitment of participants will be conducted by specifically trained child welfare staff (these so-called child welfare project coordinators receive a workshop from the project staff) in the respective programs. We will use the following recruitment strategies: (1) The general staff in the child welfare program will be invited to a digital information session on the study with all its components (e.g., assessment, treatment, collaboration with study centers). (2) The child welfare project coordinator and trained child welfare staff will organize information meetings with potential study participants to inform them about the project before the first assessment. (3) Information material on the project (poster, flyers, or postcards) will be made available for children and youth in the child welfare program.

To recruit therapists, we will build collaborations with certified training institutes. The following recruitment strategies will be implemented to identify therapists for the CBITS implementation: (1) We will inform the leaders in the study centers about the study and discuss potential recruitment strategies with them. (2) We will establish cooperation agreements with the study centers in which each of them agrees to help recruit at least eight therapists for the study. In this agreement, we will specify the benefits for the therapists for their education program (e.g., CBITS group therapy sessions and case consultations will be part of their regular education) on the one hand and financial incentives on the other hand. We will further specify the (financial) benefits of the center for recruiting therapists. (3) Information material on the project (poster, flyers, or postcards) will be made available for therapists at the cooperating centers. (4) We will offer digital information meetings for interested therapists on the study, the intervention, and their tasks.

General additional recruitment efforts will include a study website, press interviews, distribution of flyers, publications in newspapers and journals, and presentations at national and international scientific conferences.

### Participants and eligibility criteria

#### Criteria for participants

The inclusion criteria for participants are (1) ages 8–16 years, because this age range reflects the age range in the CBITS evaluation studies, and this age range is specified in the CBITS manual and toolkit; (2) having experienced at least one traumatic event (based on DSM-5 or ICD-10/ICD-11 criteria) as CBITS is designed for children and adolescents with a trauma history; and (3) at least moderate PTSS (at least 21 points on the CATS-2) as this is recommended in the intervention manual. Participants do not have to fulfill the PTSD criteria as the manual does not name this a pre-condition for participation. Additionally, there is large evidence that also youth with subthreshold PTSS show high functional impairment but respond very well to trauma-focused interventions; (4) being currently cared for by a child welfare program (safe and stable living conditions), planned further stay in the program for at least 12 months in order to complete the CBITS intervention and 10-month follow-up; and (5) willingness and informed assent/consent of the participant as well as informed consent of the caregiver/legal guardian to participate in the study (sufficient motivation for group intervention and compliance with the study design).

In order to assure a high external validity of the study, we will apply only very few exclusion criteria: (1) current psychosis for safety reasons and because, in this case, another intervention has priority (same explanation for 2–4); (2) severe harm to self or others; (3) severe substance disorder; (4) acute suicidality; and (5) severe mental retardation as there is a certain necessity of sufficient cognitive abilities to benefit from CBITS, to recall trauma memories and to create a trauma narrative.

#### Criteria for therapists

In order to be able to complete the CBITS training program and to deliver the intervention, potential study therapists at the participating study centers in Ulm, Bochum, Mannheim, and Marburg have to meet the following inclusion criteria: (1) have sufficient English language skills to complete web-training and follow the 3-day training workshop as well as case consultations; (2) be enrolled in the psychotherapy training program at one of our study centers for at least another 6 months; (3) at least 1 year of psychotherapy training to have sufficient prior cognitive behavioral therapy (CBT) experience to conduct the intervention; and (4) complete written informed consent.

### Sample size

Based on the literature and our planned analyses on the effectiveness of CBITS for children, we expect a moderate effect size of *d* = 0.7 for the CBITS intervention. An attempt was made to estimate the likely effect size based on longitudinal studies reporting on children and adolescents living in the child welfare system: In our own trial of unaccompanied refugee minors, we found an effect size of *d* = 0.15 for routine care in child welfare programs [18]. A Swiss study investigating externalizing behavior problems in institutionalized adolescents over the course of 1 year found effects of *d*_girls_ = 0.28 and *d*_boys_ = 0.24 [19]. Another study investigating emotional and behavioral symptom trajectories of children in long-term out-of-home care in an English local authority found that the largest trajectories were chronic symptom profiles, in which young people were rated in the abnormal range from their first year in care and remained in this range (based on the descriptive statistics reported we calculated *d* = 0.02–0.1 for emotional problems [20]). Based on these studies, we assume a mean effect size of *d* = 0.1 for routine care for children in child welfare programs. As children and adolescents randomized to TAU + will also receive a report with a treatment indication, we assume that a small proportion in TAU + condition (10–20%) will find their way to local service providers. For those receiving psychotherapeutic treatment from local service providers, we assume a mean effect size of *d* = 1.0 based on therapy as usual conditions in other trials (e.g., [21]). In sum, based on the before-mentioned literature on routine care in child welfare systems and the assumption that a small proportion will receive treatment at local service providers, we assume an overall mean effect size of *d* = 0.3 for the TAU + condition. Following the expected effect size of *d* = 0.7 for CBITS and *d* = 0.3 for TAU + , we assume a controlled effect size of *d* = 0.4 between conditions at 4-month follow-up (T1) in favor of CBITS on the primary measure of PTSS (CATS-2). A power analysis conducted with G*Power for the within-(time)-between-(condition)-interaction requiring a power of 0.80 and *α* = 0.05 (two-tailed), a correlation of *r* = 0.3 among replicated measures (based on our previous own RCTs [18, 22]) estimates a sample size of *N* = 72 (*n* = 36 per condition) to detect the controlled effect size of *d* = 0.4 for the primary outcome between conditions. With an assumed dropout rate of about 20% across both conditions, an oversampling of *n* = 18 participants is needed, resulting in an overall sample of *N* = 90 participants (*n* = 45 per condition; *n* = 22–23 per participating site).

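### The stated 80% power is wrong: N = 72 matches an interaction effect twice the one assumed, and for d = 0.4 the planned test has about 29% power

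*Protocol article*

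**What the plan says.** The Sample size section starts from within-arm effects: "Following the expected effect size of *d* = 0.7 for CBITS and *d* = 0.3 for TAU"+. Their difference becomes the planning effect: "we assume a controlled effect size of *d* = 0.4 between conditions at 4-month follow-up (T1) in favor of CBITS". The calculation is described as "A power analysis conducted with G*Power for the within-(time)-between-(condition)-interaction requiring a power of 0.80", with alpha "0.05 (two-tailed), a correlation of" r = "0.3 among replicated measures". The result is that it "estimates a sample size of *N* = 72 (*n* = 36 per condition) to detect the controlled effect size of *d* = 0.4". An assumed 20% dropout raises this to 90 randomised, 45 per arm.

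The Statistical analysis section makes the same contrast the primary test: a mixed model with group, time (T0 and T1 only) and their interaction, with an unstructured covariance matrix. The article states neither the value of f entered in G*Power nor the SD by which 0.7, 0.3 and 0.4 are standardised.

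**The concern.** Every input except f is printed, so the claim can be checked. A sample of 36 per arm is small for 80% power at d = 0.4. A plain two-sample comparison at T1 would need 200 in total, and analysing change at a correlation as low as 0.3 is less efficient than that, not more. The likely cause is that d was converted to f by the rule for one comparison of two means and then used for an interaction, where the same d gives an f half as large.

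H1 is the only hypothesis not labelled exploratory. If the sponsor's assumptions are true, a reader is told that the trial will miss the effect 2 times in 10, when the planned test would miss it about 7 times in 10. A null result believed to come from a trial with 80% power invites the conclusion that CBITS does not work. The Background already cites a randomised trial (N = 249) of an extended version of CBITS in adolescent girls in child welfare that was not superior to usual care, and the Dissemination section intends the findings to inform policymakers.

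**Working it through.** **Inputs (Sample size and Statistical analysis sections).** Two-sided alpha 0.05; target power 0.80; changes of 0.7 and 0.3 SD; r = 0.3; k = 2 groups; m = 2 time points; 1:1 allocation; N = 72 evaluable. Taken as assumptions: equal means at T0, equal SDs at T0 and T1, and d in units of the raw-score SD.

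**1. Reproducing the plan's figure.** For the within-between interaction, G*Power uses a noncentral F with λ = N·m·f²/(1 − r), df1 = (k − 1)(m − 1) and df2 = (N − k)(m − 1). With f = d/2 = 0.2:

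- N = 70: λ = 70 × 2 × 0.04/0.7 = 8.00, power 0.796
- N = 72: λ = 72 × 2 × 0.04/0.7 = 8.23, power 0.808

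The smallest even N reaching 0.80 is 72, as printed. The dropout step, 72/0.8 = 90, is also correct. Near alternatives do not give 72:

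| Variant | N |
|---|---|
| f = 0.2, three time points | 58 |
| f = 0.2, r = 0.5 | 52 |
| f = 0.2, one-sided | 56 |
| f = 0.2/√2 | 140 |
| f = 0.2, between-group factor, m = 2 / m = 3 | 130 / 108 |
| f = 0.1 | 278 |

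**2. The f implied by the plan's effect.** In SD units the cell means (T0, T1) are 0 and −0.7 for CBITS, and 0 and −0.3 for TAU+. After removing the grand mean and both main effects, the interaction deviations are +0.1 and −0.1 for CBITS and −0.1 and +0.1 for TAU+. Their root mean square is f = 0.1, that is d/4. Conversely, f = 0.2 is a difference in change of 4 × 0.2 = 0.8 SD.

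**3. Power with f = 0.1.**

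- N = 72: λ = 72 × 2 × 0.01/0.7 = 2.06, power 0.293
- N = 90, no dropout: λ = 2.57, power 0.354
- 80% power: N = 278 evaluable (power 0.802), or 278/0.8 ≈ 348 randomised

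**4. Independent check.** With two time points and unstructured covariance, the interaction test is a test of the difference in change. SD of change = √(2(1 − 0.3)) = 1.183, and the standardised difference is 0.4/1.183 = 0.338. A t test with 36 per arm has power 0.293 and needs 139 per arm for 80%. A simulation of 20,000 trials gave 0.294.

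**5. More favourable readings of d = 0.4.**

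| Analysis | Standardised effect | Power, N = 72 | Power, N = 90 | N for 80% |
|---|---|---|---|---|
| Difference in change (planned test) | 0.4/√1.4 = 0.338 | 29% | 35% | 278 |
| T1 only, or d in SDs of change | 0.400 | 39% | 47% | 200 |
| Baseline-adjusted (ANCOVA) | 0.4/√(1 − 0.3²) = 0.419 | 42% | 50% | 182 |

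**6. Detectable difference at N = 72 with 80% power.** 0.79 SD for the planned test; 0.64 SD with baseline adjustment. For the planned test to have 80% power at 0.4 SD, r would have to be about 0.82; r = 0.7 gives 58%.

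**The case against.** The value f = 0.2 is inferred, since the article prints no f. That is fair: the text supports saying that N = 72 is consistent with f = d/2, not that this input is documented. An uneven value such as f = 0.18 with three time points would also return 72. However, the primary test uses two time points, and 0.18 has no evident link to d = 0.4. The finding does not depend on the inferred cause, because none of the readings of d = 0.4 tried above gives 80% power at N = 72.

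The 29% is also the low end of a range. It takes d in raw-score SDs and assumes equal SDs at T0 and T1, although the entry threshold of 21 points on the CATS-2 may narrow the baseline SD. If the T0 SD were 0.8 of the T1 SD (an illustrative assumption), the SD of change would be √(1 + 0.64 − 2 × 0.3 × 0.8) = 1.077 and power about 34%. The planned covariate analysis includes pre-treatment PTSS, and the mixed model uses every randomised participant, so 72 is a planning floor. All of this stands, and the range is 29–42% at N = 72 and 35–50% if all 90 are observed. None of it approaches 80%.

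Finally, the article commits to publishing regardless of significance and to reporting Cohen's d, which lessens the risk of misreading. It does not correct the stated power.

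**Conclusion.** The concern holds, and the power statement must be corrected. Under the plan's own inputs (0.4 SD difference in change, r = 0.3, two-sided alpha 0.05), the planned interaction test has about 29% power at 72 evaluable and 35% at 90, against a stated 80%. The stated power would apply to a difference of about 0.8 SD, twice the assumed effect. The most favourable standard analysis, adjusted for baseline, reaches 42% and 50%.

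The 29% rests on equal baseline means (reasonable given stratification by CATS-2), equal SDs at both times, and d in raw-score SDs; relaxing the last two does not change the conclusion. Clustering within CBITS groups is left out because the article gives no intraclass correlation. Positive clustering would be expected to lower power further, by an amount that cannot be stated from the document.

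**What to change.** Rewrite the power sentence in the protocol, and in the SAP if it repeats the figure:

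- State the f used, and the SD by which 0.7, 0.3 and 0.4 are standardised.
- Give the corrected power for a 0.4 SD difference in change: about 29% at 72 evaluable with the group-by-time interaction, or about 42% with baseline adjustment (35% and 50% if all 90 are observed).
- Give the difference detectable with 80% power at 72 evaluable: 0.79 SD, or 0.64 SD with baseline adjustment.
- State that H1 will be reported as an estimate with a 95% confidence interval, and that a non-significant result will be read as inconclusive rather than as evidence of no benefit.

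The cost is an amendment to the text and a much less favourable stated power. No further participants are needed to correct the statement, but the correction does not restore 80% power. Whether to enlarge the trial, move to a baseline-adjusted primary analysis, or proceed with the limitation disclosed is for the sponsor to decide.
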